### Participant Withdrawal

All participants meeting study inclusion will be included in this study. Whole of service hospital use data from medical records will be used as the primary data source. Participants will be withdrawn if they are considered outliers by the data control panel. Outliers include those who have been recorded as using health services in a non-standard way e.g. very rarely a patient is given different care packages such as a long term residential stay that is independent of clinical need due to pressure on housing or specific sensitivities (e.g. justice involvement).

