### Number of Participants

It is expected that at least 70 participants will be involved in the study (35 in the intervention group and 35 in TAU control).

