### Primary Outcomes

11.1 Primary Outcome

The primary outcome involves the change in hospital use measured by audit of medical record admission and discharge data. Specifically, number of presentations to the inpatient unit, number of bed days in the inpatient unit, and number of presentations to the emergency department. Secondary analyses will involve ratings of severity of diagnostic symptoms and changes in staff confidence and skills.

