### Handling of Withdrawals and Losses to Follow-Up

Participants who have been withdrawn from either condition will be removed from the study and documentation with regards their withdrawal will be held by the data control panel.

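### A panel may withdraw patients as outliers on recorded service use, the source of the primary outcome, under an open criterion with no decision time and no masking to site

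*Protocol*

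**What the plan says.** Participant Withdrawal (section 16) opens with "All participants meeting study inclusion will be included in this study". It then says "Participants will be withdrawn if they are considered outliers by the data control panel". The definition that follows is "Outliers include those who have been recorded as using health services in a non-standard way", illustrated by the remark that "very rarely a patient is given different care packages such as a long term residential stay that is independent of clinical need", with housing pressure and justice involvement given as reasons.

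Handling of Withdrawals and Losses to Follow-Up (section 17) states the consequence: "Participants who have been withdrawn from either condition will be removed from the study". The panel keeps documentation of each withdrawal.

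Primary Outcomes (section 11) says "The primary outcome involves the change in hospital use measured by audit of medical record admission and discharge data", and names the components as "number of presentations to the inpatient unit, number of bed days in the inpatient unit, and number of presentations to the emergency department". The Statistical Analysis Plan section puts the emphasis on the interaction of time with site.

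**The concern.** The variable on which a patient can be excluded and the variable on which the trial is judged come from the same hospital records. An exclusion decided by judgement on those records can depend on the outcome. Each site is one arm, so any difference between sites in how the judgement is made coincides with the treatment comparison.

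Section 16 also contradicts itself: a patient who meets the inclusion criteria cannot both be included without exception and be withdrawn on a panel's opinion.

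The whole patient is removed. Emergency presentations and admissions that have nothing to do with the unusual stay are lost with it. With about 35 patients per group and skewed bed days, one or two removals can move a site mean noticeably.

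**Working it through.** **What the rule leaves open.** Reading sections 11, 16, 17 and the Table of Procedures Schedule together:

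- Criterion: no threshold and no closed list. The wording introduces examples only.
- Timing: none stated. Use is monitored in both 18-month periods, so a decision could rest on baseline records, follow-up records or both.
- Masking: nothing hides site from the panel.
- Retention: section 17 removes the patient, and the protocol states no analysis that keeps them.

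The protocol has no figure of its own to reproduce here. It gives no SD, effect size or power, and sets the sample by the number of eligible inpatients.

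**Illustration under no effect.** From the protocol: 35 per group (Number of Participants) and two periods. Assumed: mean μ = 15 bed days in each period at both sites; Poisson counts with a gamma patient effect (shape 1) and a gamma period effect (shape 1); patients independent within site; no entry condition modelled.

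These assumptions imply:

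- Variance of bed days = μ + μ²[(1+1)(1+1) − 1] = 15 + 225 × 3 = 690. SD = 26.3, or 1.75 × 15.
- Covariance between periods = μ² × 1 = 225. Correlation = 225/690 = 0.33.
- Variance of a patient's change = 2 × (690 − 225) = 930.
- Variance of the difference in mean change between sites = 930 × (1/35 + 1/35) = 53.1. SD = 7.3 days.

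Simulation used 20,000 replicates and a two-sided 5% t test on change. The last column counts significant results in favour of the intervention.

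| Removed | Mean shift in difference in change | Shift / 7.3 | False positives favouring intervention |
|---|---|---|---|
| Nobody | about 0 | 0 | 2.1% |
| Heaviest follow-up user, intervention site only | −1.97 days | 0.27 | 4.1% |
| Heaviest two, same site | −3.06 days | 0.42 | 5.9% |
| Heaviest three, same site | −3.80 days | 0.52 | 7.8% |
| Same follow-up rule at both sites | about 0 | 0 | not materially changed |
| Heaviest on total use over both periods, one site only | about 0 | 0 | not materially changed |

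As a share of the assumed mean, the shifts run from 1.97/15 = 13% to 3.80/15 = 25%.

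**Other inputs.** With mean 20 bed days, gamma shape 0.3 or 1.0 and a between-period correlation of about 0.15 or 0.45-0.49, removing one to three of the heaviest follow-up users at the intervention site gave shifts of about −0.7 to −5.6 days. False positives favouring the intervention were 3.8% to 9.8%. Removing the heaviest baseline users there gave +0.7 to +5.5 days, against the intervention. Removing one patient from each site by the same rule, or removing on total use, again gave about zero bias.

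**The case against.** The strongest defence is that the rule concerns why a bed was occupied, not how much it was used. The stated examples are stays with a non-clinical cause, and they are called very rare. A housing placement counted as bed days can fairly be seen as contamination of a clinical endpoint. That aim is reasonable and stands. It does not close the list, and it does not require removing the whole patient.

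A reader might infer that the protocol prescribes removal of the heaviest users after allocation, and so builds a bias into the result. The documents do not support that. Nothing ranks patients by use, the rule applies to both conditions, and with no timing stated the decision could be made from baseline records. The illustration is close to a worst case. Three of 35 is 8.6% of a site, which is hard to square with very rare, and even then the shift is about half an SD of the estimate. Removal applied alike at both sites cancels in the interaction. It would still create an apparent fall within each site (about 2.0 days when the heaviest follow-up user is removed from each), but the within-site change is not the main comparison.

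A separate analysis plan, not available here, might define criteria, masking or a sensitivity analysis. It would not undo the removal, because the protocol itself fixes that. Keeping documentation helps an audit but returns nobody to the analysis.

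**Conclusion.** The concern holds as a matter of what the rule permits. Sections 16 and 17 allow patients to be excluded on the endpoint, at the panel's discretion, after outcomes are known, and they conflict with the opening sentence of section 16. Bias in the interaction needs two conditions together: removals that differ by site, and selection on one period. The protocol prevents neither.

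The upper illustration is a shift of about -2 to -4 bed days against an SD of about 7 days, with false positives favouring the intervention rising from about 2% to 4-8%. It rests on the assumed mean, spread, correlation and independence of patients, on one-sided removal of the heaviest follow-up users, and on a t test on change in place of the planned mixed model. It shows possible bias, not expected bias. The stronger claim that the trial's result will be biased by this rule cannot be drawn from the protocol.

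**What to change.** Delete the withdrawal of outliers from the primary analysis. State that every participant who meets the inclusion criteria is kept and analysed by baseline site, which also removes the contradiction within section 16, and amend section 17 to match.

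If stays unrelated to clinical need are a concern, report an analysis excluding them only as a sensitivity analysis. The criterion should be closed and objective, fixed before follow-up data are extracted, and applied to both sites by staff masked to site. Report counts and reasons by site.

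The cost is a short amendment to two sections. The downside is somewhat more variable bed days in the primary analysis.

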### Handling of Withdrawals and Losses to Follow-Up

Participants who have been withdrawn from either condition will be removed from the study and documentation with regards their withdrawal will be held by the data control panel.

# Procedures Schedule

### Table of Procedures Schedule

CONTROL SITE INTERVENTION SITE

| **STUDY PERIOD** | **0-18 months**  **TAU BASELINE** | **Wash-out**  **1 month** | **19-36 months**  **TAU F/UP** | **0-18 months TAU BASELINE** | **Wash-out**  **1 month** | **19-36 months**  **Intervention**  **F/UP** |
| --- | --- | --- | --- | --- | --- | --- |
| **Recruitment of inpatients with diagnosis of personality disorder** | X |  |  | X |  |  |
| **Monitoring of Emergency use** | X |  | X | X |  | X |
| **Monitoring of inpatient bed days** | X |  | X | X |  | X |

NOTE: Washout is a one month transition between baseline monitoring (both groups) and commencement

of the stepped care model in the intervention group

# Adverse Event Reporting

### Assessment and Documentation of Adverse Events

Adverse events are likely to involve sentinel events in the health service concerning people diagnosed with personality disorder. Critical incidents and other events will be managed by (a) normal clinical governance protocols involving the involvement of senior managers and the clinical director, and (b) referral of incidents to the ethics governance unit of the health service for referral to the institutional review board. The IRB will contact researchers and seek responses to critical incidents in relation to the safe and effective conduct of the trial.

# Statistical Methods

### Sample Size

The sample size will be determined on the basis of the number of inpatients meeting the study criteria within the 18 month baseline recruitment period. All participants within the study catchment presenting for services to the health service and thus captured in the digital medical records system will be included if they meet the study inclusion criteria.

### Statistical Analysis Plan

The statistical analysis plan is to evaluate the use of health care resources across the study sites with particular attention on time x intervention site interactions. The general linear model will be employed, specifically a mixed models analysis, with the covariance structure for residuals specified as ante-dependent (first order).

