# Investigators and Facilities

### Study Location/s

The study involves the following locations in Australia:

*Researcher Location:*

The researchers are based at the University of Wollongong.

*NSW Health Location:*

The intervention clinicians are in the South Eastern Sydney and Illawarra Health service. The two study locations are centred on the Shellharbour hospital precinct and surrounding mental health units and services, and the St George/Prince of Wales hospital precinct and surrounding mental health units and services. The two services are similar in catchment size, staffing and clinical flow through; but are separated by a national park and natural landforms ensuring they are also serving distinct populations with separate staff servicing each precinct. This minimises contamination between sites.

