# Study Objectives

### Primary Objectives

The aim of this study is to evaluate the efficacy of a whole of service approach to personality disorders.

We will assess the impact of the implementation compared to TAU on a service level.

Clinical patients will therefore get the standard care offered in their service, however the care will vary between sites. One site will implement the intervention (whole of service approach), whereas the other will continue with standard treatment as usual.

We will study the impact of the intervention by using hospital records (inpatient admissions and emergency department presentations).

The study has two aims: (1) to assess the impact of the implementation compared to TAU on a service level, using hospital records (primary outcome), and (2) to assess the impact of the implementation on individual patient outcomes and therapist knowledge and attitudes (secondary outcomes).

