### Preliminary Study Design Diagram

**CONSORT Flow Diagram**

Randomized – 2 sites

Assessed for eligibility – 2 sites

18 month baseline

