# Participant Enrolment and Randomisation

### Recruitment

Participants will be clients of the health service with a diagnosis of personality disorder who have been admitted to the inpatient unit within the baseline 18 month study period.

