### Inclusion Criteria

The inclusion criteria are clients having a primary diagnosis of ICD-10 personality disorder who are a mental health inpatient of the Health Service within the 18 month baseline recruitment period. They must be aged 12 or over.

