### Randomisation Procedures

The study will use a computer generated randomisation sequence to allocate study sites to intervention or control. The randomisation will be performed independently from the health service and the sites.

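### Only two sites are randomised, so patient characteristics are not balanced by design; the stated time x site contrast should cross period with age, sex and diagnosis group

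*Protocol*

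**What the plan says.** Under Randomisation Procedures the unit of allocation is the site: "The study will use a computer generated randomisation sequence to allocate study sites to intervention or control". The flow diagram gives the number of units as "Randomized – 2 sites", and Primary Objectives confirms one per arm: "One site will implement the intervention (whole of service approach), whereas the other will continue with standard treatment as usual".

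Study Location/s gives the only statement of comparability: "The two services are similar in catchment size, staffing and clinical flow through". The same sentence adds that the precincts are geographically separated, "ensuring they are also serving distinct populations with separate staff servicing each precinct". It says nothing about age, sex, diagnosis or severity.

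Eligibility is wide. Inclusion Criteria accepts any primary ICD-10 personality disorder, and on age says "They must be aged 12 or over". Recruitment takes clients "admitted to the inpatient unit within the baseline 18 month study period".

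Section 21 (Statistical Analysis Plan) describes a general linear mixed model with first-order ante-dependent residuals, "with particular attention on time x intervention site interactions". It names no patient covariate, and it neither rules one in nor rules one out.

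**The concern.** A patient's arm is decided by catchment. With two randomised units, the allocation cannot be expected to balance anything about the patients, so the comparison depends on how change over time is modelled.

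A time x site contrast removes any difference between sites that stays constant across the two periods. It leaves in any difference in case mix that goes with a different natural course. A site with more young patients, or a different mix of disorder types, could show a larger fall in admissions, bed days or emergency presentations with no help from the intervention, and the contrast would credit that fall to the treatment. The bias does not shrink as the cohort grows, whereas the standard error does. Sections 9 and 20 set a floor of 70 and otherwise take every eligible inpatient.

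This part of the problem comes from recorded characteristics, so the analysis can address it. Drift that belongs to a site and is not recorded is a separate matter, and no patient covariate removes it.

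**Working it through.** **Inputs from the protocol.** Two sites, one per arm (Primary Objectives; flow diagram; section 15). At least 35 + 35 = 70 participants (section 9). Two 18-month periods (section 10). Contrast: time x site (section 21). The protocol gives no case-mix figures, effect size, standard deviation or significance level, so there is no stated figure to reproduce. All case-mix inputs below, and the two-sided 5% level, are assumptions.

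**Test used.** With one baseline and one follow-up value per patient, the time x site test is a two-sample t-test on change. The protocol does not give the number of time points. The ante-dependence structure differs from an unstructured covariance only when there are more than two.

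**Step 1: an age example.** Assume use falls by 60% in patients under 25 (multiplier 0.4) and by 20% in older patients (0.8), with no treatment effect.

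| Under 25, site A v site B | Follow-up/baseline, A | Follow-up/baseline, B | Spurious ratio |
|---|---|---|---|
| 40% v 20% | 0.40×0.4 + 0.60×0.8 = 0.64 | 0.20×0.4 + 0.80×0.8 = 0.72 | 0.64/0.72 = 0.89 |
| 35% v 25% | 0.35×0.4 + 0.65×0.8 = 0.66 | 0.25×0.4 + 0.75×0.8 = 0.70 | 0.66/0.70 = 0.94 |
| 30% v 25% | 0.30×0.4 + 0.70×0.8 = 0.68 | 0.70 | 0.68/0.70 = 0.97 |

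**Step 2: false positives.** Simulation under no effect: baseline count 1 + Poisson(λ), with λ gamma of mean 2 and shape 1; follow-up count Poisson((1 + λ)×multiplier). Mean baseline use is 1 + 2 = 3, so the 40% v 20% mix gives a spurious difference in mean change of 3×(0.64 − 0.72) = −0.24 events.

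- 40% v 20%, 35 per site: 6.7% (1,500 trials) and 7.3% (3,000 trials). Allowing for simulation error, about 7% to 8%. With age in the change model: 4.3% and 4.6%.
- 35% v 25%, 35 per site: 5.5%.
- 30% v 25%, 35 per site: 4.7%, which is nominal.
- Larger cohorts, sizes assumed: 40% v 20% gives about 17% at 150 and 25% at 300 per site, and 4% to 6% with age in the model. At 300 per site, 30% v 25% gives 6.9%.

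**Step 3: the same point without a particular covariate.** Let d be the site difference in a covariate in SDs, and r its correlation with change. The bias is d×r SDs of change, and the false-positive rate is P(|Z + d·r/√(2/n)| > 1.96).

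- d = 0.5, r = 0.3, n = 35: bias 0.15; √(2/35) = 0.239; 0.15/0.239 = 0.63; rate 9.6%. Simulation: 9.4% unadjusted, 5.7% adjusted.
- d = 0.2, r = 0.2, n = 35: bias 0.04; rate 5.3%.
- d = 0.8, r = 0.5, n = 35: bias 0.40; rate 38.7%.
- d = 0.5, r = 0: no bias; 5.0% unadjusted and 4.8% adjusted.

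**Step 4: is time since the qualifying admission a usable covariate?** Recruitment covers months 0 to 18 and follow-up opens at month 19, so this lag runs from 1 to 19 months and may predict change. It is, however, derived from admissions, which are part of the primary outcome. Take the qualifying admission as the first in the window, and assume stable gamma-Poisson admission rates, no effect, and entry conditional on at least one baseline admission. Time to first admission then correlates about −0.45 with the baseline admission count. When sites differ only in mean rate, adding the lag enlarges the spurious site difference in change:

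| Mean rates, site A v B | Without lag | With lag |
|---|---|---|
| 1 v 2 | 0.16 | 0.24 |
| 1.5 v 2.5 | 0.13 | 0.19 |
| 2 v 4 | 0.14 | 0.25 |

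The rates are assumed, but the mechanism follows from how the lag is defined.

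**The case against.** **A covariate list belongs in a statistical analysis plan, which may exist separately.** This stands in part. Section 21 gives the interaction as its focus and excludes nothing. But it carries the heading of an analysis plan, points to no other document, and goes as far as fixing the residual covariance. The point is also more than a request to name covariates: with whole sites allocated, the stated contrast is open to a bias that a better model of the same records would reduce.

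**A reader might infer from the wording on separate populations that case mix is known to differ.** The documents do not support that. In Study Location/s the phrase argues against contamination, meaning that catchments do not overlap. The protocol asserts neither imbalance nor balance in patient characteristics, and the point needs only the absence of any balancing mechanism.

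**The size is modest at the stated number.** This stands. At 35 per site, even a two-fold age imbalance with sharply different natural courses gives about 7% to 8%, and milder mixes give about 5%. The rates near 17% and 25% need 150 and 300 per site, which the protocol never states.

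**Staggered entry before a common follow-up start might seem to call for adjustment for the lag.** Both sites follow the same calendar, so the lag matters only if accrual timing differs between them, and nothing in the protocol suggests that it does. Adjusting for it can also add bias (Step 4).

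**Treatment is fully confounded with site whatever is adjusted.** True. Adjustment deals only with the recorded part and does not make two sites into a well-replicated comparison.

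**Conclusion.** The concern holds in a limited form. Site allocation balances no patient characteristics, and the contrast stated in section 21 removes differences in level but not recorded differences that predict change. Whether such differences exist, and how large they are, cannot be learned from the protocol. Under the assumed 40% v 20% age mix and natural falls of 60% v 20%, the false-positive rate at 35 per site is about 7% to 8% instead of 5%. It is close to 5% under milder imbalance, and higher only if the imbalance or the cohort is much larger than assumed. These figures rest on a two-period change analysis that treats patients as independent.

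It would go too far to conclude that the trial's result will be biased by case mix, or that adjustment would make the comparison unconfounded. The documents support only that the stated model leaves an avoidable route for bias open.

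**What to change.** In section 21, state the test model as period, site and period x site, plus period crossed with age at month 0, sex and ICD-10 code group. If the cohort is near 70, keep age only. The covariates must be crossed with period: entered as main effects in a two-period model with complete data, they leave the period x site estimate unchanged. Report the unadjusted interaction beside the adjusted one.

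In section 22, list age, sex and diagnosis code among the fields to extract. Age and diagnosis are already needed to establish eligibility, and all three would come from the hospital records being pulled.

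Do not include months from the qualifying admission as a covariate.

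The cost is protocol wording, a few model parameters, and a slight loss of precision if the covariates do not predict change. Confounding of treatment with site and unmeasured site drift remain, and the report should say so.
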